## Abstract

**Introduction::**

(Neo-)adjuvant chemotherapy for breast cancer has a deleterious impact on muscle tissue resulting in reduced cardiorespiratory fitness, skeletal muscle mass and function. Physical exercise during treatment may counteract some of these negative effects. However, the effects of resistance training (RT) alone have never been explored. The present study aims to investigate if heavy-load RT during (neo-)adjuvant chemotherapy counteracts deleterious effects on skeletal muscle in women diagnosed with breast cancer. We hypothesize that (neo-)adjuvant treatment with chemotherapy will reduce muscle fiber size, impair mitochondrial function, and increase indicators of cellular stress and that RT during treatment will counteract these negative effects. We also hypothesize that RT during (neo-)adjuvant chemotherapy will increase muscle and blood levels of potential antitumor myokines and reduce treatment-related side effects on muscle strength and cardiorespiratory fitness.

**Methods::**

Fifty women recently diagnosed with breast cancer scheduled to start (neo-)adjuvant chemotherapy will be randomized to either randomized to either intervention group or to control group.

The intervention group will perform supervised heavy-load RT twice a week over the course of chemotherapy (approximately 16-weeks) whereas the control group will be encouraged to continue with their usual activities. Muscle biopsies from *m. vastus lateralis* will be collected before the first cycle of chemotherapy (T0), after chemotherapy (T1), and 6 months later (T2) for assessment of muscle cellular outcomes. The primary outcome for this study is muscle fiber size. Secondary outcomes are: regulators of muscle fiber size and function, indicators of cellular stress and mitochondrial function, myokines with potential antitumor effects, muscle strength, and cardiorespiratory fitness.

**Ethics and dissemination::**

Ethical approval has been obtained from the Regional Ethical Review Board in Uppsala, Sweden (Dnr:2016/230/2). Results will be disseminated through presentations at scientific meetings, publications in peer-reviewed journals, social media, and patient organizations.

**Trial registration number::**

NCT04586517.

## Introduction

1

The increasing survival rates of women diagnosed with breast cancer requires an increased focus on measures to counteract persistent adverse effects of treatment. Neo-adjuvant treatment aims to decrease tumor burden before surgery and adjuvant treatment to inhibit proliferation in eventual remaining cancer cells after surgery. A common (neo-)adjuvant treatment for women with breast cancer is combined chemotherapy with anthracyclines and taxanes, given in 3 cycles of each chemotherapy type with a recovery period after each cycle.^[1]^ Anthracyclines have a cardiotoxic effect^[2,3]^ and previous observational studies have shown approximately 10% decrease in maximal oxygen uptake (VO_2max_) during chemotherapy.^[4]^ VO_2max_ is determined by both central- (e.g., cardiac function) and peripheral factors (e.g., skeletal muscle function) and reductions in VO_2max_ are common in patients with breast cancer without any signs of impaired cardiac function.^[5]^ This suggests that there may be changes in peripheral factors affecting oxygen transport, however, this must be further elucidated. Direct negative effects of chemotherapy on skeletal muscles are documented in animal studies, where anthracyclines impair force-generating capacity and mitochondrial function in skeletal muscles.^[6–9]^ These findings are supported by analysis on muscle biopsies from patients with prostate cancer,^[10]^ testicular cancer,^[11]^ and in 2 small-scale studies on patients with breast cancer undergoing chemotherapy.^[12,13]^ The effects of treatment with taxanes on skeletal muscle are less studied. However, muscle and joint pain, referred to as “taxane acute pain syndrome”^[14]^ is commonly reported and occurs about 24 to 48 hours after treatment and lasts for about 5 to 7 days.^[15]^ Altogether, previous studies confirm the deleterious effects of chemotherapy on muscle size, mitochondrial structures, and muscle function. An alternative reason for these muscle changes could be reduced levels of physical activity, which is common in patients with cancer.^[16]^ Epidemiological studies have found that patients receiving chemotherapy decrease their level of physical activity during treatment, and this reduction may still be present after the end of the treatment period.^[17,18]^ Regardless of cause, loss of skeletal muscle mass has been associated with reduced physical functioning and increased toxicity, that is poor tolerance to chemotherapy, and consequently worse prognosis.^[19,20]^

Over the past decades, physical activity has emerged as an important factor to improve cancer outcomes and international guidelines recommend patients to engage in regular physical activity.^[21]^ In women with breast cancer, physical exercise (i.e., planned, structured physical activity aiming to improve/sustain physical function and fitness^[22]^), has been shown to reduce the loss of muscle strength, which is commonly observed during and/or after treatment.^[23]^ Possible protective effects of physical exercise on skeletal muscle during chemotherapy for breast cancer have only been studied in 1 previous study. Mijwel and colleagues^[13]^ showed that participating in a training program that combined high-intensity-intervals with either resistance training (RT-HIIT) or moderate-intensity aerobic exercise (AT-HIIT) during treatment prevented a decrease in muscle fiber size in both intervention groups in comparison to the control group (patients receiving usual care).^[13]^ In addition, participants in the RT-HIIT group showed a greater increase in muscle fiber size and satellite cell (SC) content in comparison to participants in the AT-HIIT. These results indicate that RT on its own could have a potentially protective effect on skeletal muscle function and size in breast cancer patients undergoing chemotherapy. Resistance training during chemotherapy may also improve treatment efficiency, quality of life and reduce cancer-related fatigue, and other side effects of treatment,^[24,25]^ some of these improvements may be related to increased production of anti-tumor myokines in the exercising muscles.^[26]^ The effects of RT alone on muscle cellular outcomes during chemotherapy however, have not yet been investigated in women with breast cancer.

The *aim* of this study is to investigate the effects of heavy-load RT on muscle cellular outcomes in women with breast cancer undergoing (neo-)adjuvant chemotherapy.

Our hypotheses are:

1.(Neo-)adjuvant chemotherapy will reduce muscle fiber size, muscle strength, cardiorespiratory fitness, impair mitochondrial function, and increase indicators of cellular stress.2.Resistance training during (neo-)adjuvant chemotherapy will reduce treatment side effects on muscle tissue by counteracting the negative effects on fiber size, mitochondrial function, cell stress, muscle strength and cardiorespiratory fitness.3.Resistance training during (neo-)adjuvant chemotherapy will increase muscle and blood levels of potential antitumor myokines.

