### Study design

2.1

This study is a two-armed randomized controlled trial with follow-up at 6 months (Fig. 1). Data will be collected before the first cycle of chemotherapy (T0), after chemotherapy (T1), and 6 months later (T2). The primary outcome for this study is muscle fiber size. Secondary outcomes are: regulators of muscle fiber size and function, indicators of cellular stress and mitochondrial function, myokines with potential antitumor effects, muscle strength, and cardiorespiratory fitness. All outcomes are listed in Table 1.

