### Participant recruitment and eligibility criteria

2.2

Women recently diagnosed with breast cancer will be recruited from Uppsala University Hospital.

Eligibility criteria are:

1.women diagnosed with stage I-III breast cancer,2.>18 years old,3.literate in Swedish,4.scheduled to undergo (neo-)adjuvant chemotherapy with a combination of taxanes and anthracyclines or only 1 of these treatments.

Exclusion criteria are:

1.unable to perform basic activities of daily living,2.cognitive disorders or severe emotional instability,3.other disabling comorbidities that might hamper physical training (e.g., severe heart failure, chronic obstructive pulmonary disease, orthopedic conditions, and neurological disorders).

Eligibility will be assessed by treating surgeons or medical oncologists, and all eligible women will receive written information. Women who meet the inclusion criteria will be provided with further information about the study and written informed consent will be obtained by research staff. Based on the experience gained from on-going studies and previous relevant studies within the research group, an inclusion rate of 35% to 40% can be expected. The study was initiated in December 2018 and with the expected inclusion rate; the last participants will complete the intervention during the second half of 2021.

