### Randomization

2.4

After completion of baseline measurements, participants will be randomized by research staff in a 1:1 ratio to either the *intervention group* (supervised heavy-load RT during chemotherapy treatment) or to the *control group* (activity as usual during chemotherapy treatment), stratified on treatment (neo-adjuvant or adjuvant treatment). Sealed envelopes will be used to conceal the group allocation.

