#### Muscle fiber size

2.8.1

Muscle fiber size, measured as muscle fiber cross-sectional area (CSA) represents the primary muscle cellular outcome. Muscle fiber CSA will be measured using immunohistochemistry in cross-sections of muscle biopsies. Briefly, transverse serial sections of the muscle biopsy (8 μm thick) will be cut using a cryostat microtome at −22°C and mounted on glass slides. Serial cross-sections will be immunohistochemically stained for fiber types (type I, type IIa, and IIx) for CSA measure. Muscle fiber CSA will be measured for the different phenotypes separately. Assessors will be blinded to each participant's allocation.

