### Statistical analyses

2.11

Data will be analyzed according to the intention-to-treat principle. Analyses will include standard descriptive statistics, *t* tests, correlation, regression and two-way repeated-measures ANOVA or the comparable nonparametric test as necessary to examine differences between and within groups, at T0, T1, and T2. In addition, a per-protocol analysis, that is, adherence to the protocol, will be conducted. Should imbalances in important variables be detected, sensitivity analyses will also be added including these as covariates in the model. All data will be cleaned and quality-checked before analysis.

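### Hypothesis 1 is worded as an effect of chemotherapy, but every participant receives chemotherapy, so the trial can show only change during it

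*Protocol article*

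**What the plan says.** The Introduction of the protocol article lists three hypotheses. The first is causal in form: (neo-)adjuvant "chemotherapy will reduce muscle fiber size, muscle strength, cardiorespiratory fitness, impair mitochondrial function, and increase indicators of cellular stress". The second and third concern what RT does during chemotherapy, and the stated aim concerns RT only.

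On design, section 2.1 says "This study is a two-armed randomized controlled trial with follow-up at 6 months". Section 2.2 admits women "scheduled to undergo (neo-)adjuvant chemotherapy with a combination of taxanes and anthracyclines or only 1 of these treatments". Section 2.4 defines the control condition as "activity as usual during chemotherapy treatment", and the intervention is supervised RT over the same period. Measurements are taken before the first cycle (T0), after chemotherapy (T1) and six months later (T2).

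Section 2.11 lists t tests, correlation, regression and two-way repeated-measures ANOVA, or nonparametric equivalents, "as necessary to examine differences between and within groups, at T0, T1, and T2".

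The Introduction also gives a rival explanation for muscle loss seen in earlier studies: "An alternative reason for these muscle changes could be reduced levels of physical activity, which is common in patients with cancer". It goes on to say that activity tends to fall during chemotherapy and may stay low afterwards.

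**The concern.** A claim that chemotherapy causes a loss needs a comparison with what would have happened without chemotherapy. This trial randomises RT, not chemotherapy, and everyone is exposed. The only data that bear on hypothesis 1 are before-and-after changes, and the control arm is the natural place to look for them. Those changes mix any chemotherapy effect with reduced activity and with time.

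Hypothesis 1 comes first of the three, and the first outcome it names, muscle fiber size, is the trial's primary outcome. The Discussion repeats the causal framing when it says the measurements will shed light on how chemotherapy acts on muscle. If the wording stands, a significant fall in controls could be published as proof that chemotherapy shrinks muscle fibers, when the design shows only that fibers shrank while chemotherapy was given.

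**Working it through.** **Step 1: which contrasts the design offers.**

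| Contrast | Randomised? | What it can answer |
|---|---|---|
| RT vs control, change from T0 to T1 | Yes | Effect of RT during chemotherapy (hypotheses 2 and 3) |
| Control arm, T0 to T1 | No | Change during chemotherapy, from all causes together |
| RT arm, T0 to T1 | No | As above, plus RT |
| Chemotherapy vs none | Not available | Hypothesis 1 as worded |

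The last row is empty because sections 2.2 and 2.4 place every participant on chemotherapy. The choice of analysis model does not change this.

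**Step 2: whether measured activity fills the gap.** Activity is recorded by armband for seven days at T0, T1 and T2 (section 2.10.4 and Table 1) and by training logbook (section 2.6). Adjusting for it would be an observational analysis. Among women who are all exposed to chemotherapy, it would still leave chemotherapy mixed with time. Section 2.11 describes no analysis for this purpose.

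**Step 3: how easily hypothesis 1 could be confirmed with no chemotherapy effect.** The plan gives no figure for this, so there is none to reproduce.

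Inputs:
- n = 25 controls, the planned arm size in section 2.3; n = 16, the per-arm number section 2.3 gives for 95% power, serves as a lower case for losses.
- Two-sided 5% paired t test (assumed; the article states no significance level).
- True chemotherapy effect zero (assumed).
- Mean shift in controls from other causes: d = 0.25, 0.5 or 0.75 SD of the within-person change (assumed; the documents give no value).

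Formula: the test statistic follows a noncentral t distribution with n − 1 degrees of freedom and noncentrality d√n. The probability of significance is P(|t| > critical value).

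- n = 25: critical value 2.064; noncentrality 0.25 × 5 = 1.25, 0.5 × 5 = 2.5, 0.75 × 5 = 3.75.
- n = 16: critical value 2.131; noncentrality 0.25 × 4 = 1.0, 0.5 × 4 = 2.0, 0.75 × 4 = 3.0.

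| Shift not due to chemotherapy (SD of change) | 25 controls | 16 controls |
|---|---|---|
| 0.25 | 22% | 16% |
| 0.5 | 67% | 46% |
| 0.75 | 95% | 80% |

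Almost all of this probability lies in the direction of the shift; the opposite tail is below 0.2% in every cell. A larger sample makes the misattribution more likely, because the within-arm test detects any real change whatever its cause.

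**The case against.** The strongest defence is that hypothesis 1 is background. The aim is the effect of RT, and hypotheses 2 and 3 rest on the randomised comparison, so rewording hypothesis 1 changes no estimate, sample size or primary test. The authors are also open about inactivity as a rival cause. They measure activity, ask controls to keep their habitual level, collect chemotherapy type and dose, and plan regression and covariate sensitivity analyses. All of this is true and it limits the seriousness of the point. It does not rescue the hypothesis as written, because none of these measures supplies an unexposed comparison.

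Three stronger readings are tempting, and the documents do not support them.

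- **That hypothesis 2 will be judged by a significant loss in controls and none in the RT arm.** Section 2.11 lists within-group comparisons without saying which contrast decides, so the risk exists. But it also plans between-group comparisons and a two-way repeated-measures ANOVA, whose group-by-time term tests the difference in change. Nothing states the faulty rule. Its size also depends heavily on the inputs. With equal true loss in both arms and 19 per arm (assumed, about 75% of 25), the arms would disagree on significance 29%, 50%, 23% or 3% of the time for a loss of 0.25, 0.5, 0.75 or 1.0 SD. Only half of those disagreements favour RT.
- **That fiber-size readers know the visit.** Section 2.8.1 says "Assessors will be blinded to each participant's allocation". It is silent on visit, and slide coding and batching are laboratory detail that a condensed article commonly leaves out.
- **That surgery distorts the change from T0 to T1.** Adjuvant patients have surgery before chemotherapy, so at most their recovery overlaps the interval, and no timing is given. Neo-adjuvant surgery follows chemotherapy. Surgery is a weak rival here; inactivity and time are enough.

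**Conclusion.** The point holds for hypothesis 1 only. As worded, it asks a causal question about chemotherapy that a trial with universal chemotherapy exposure cannot answer, and the protocol itself names a credible competing cause. This conclusion rests on the eligibility criteria, the arm definitions and the Introduction, and needs no assumed number. The 22%, 67% and 95% figures are illustrations: they depend on assumed shifts, a zero chemotherapy effect, a 5% two-sided test and 25 evaluable controls.

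Severity is moderate. The randomised effect of RT on muscle outcomes remains identified, and nothing here counts against it. What changes is what may be concluded from the control arm.

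**What to change.** - Reword hypothesis 1 along these lines: *muscle outcomes will decline from T0 to T1 in women receiving chemotherapy without RT*.
- Report it as the control-arm mean change from T0 to T1 with a 95% confidence interval, described as change during chemotherapy and not attributed to chemotherapy. Carry the same restraint into the Discussion.
- State in section 2.11 that effects of RT (hypotheses 2 and 3) are concluded from the randomised between-arm contrast (group by time), and that within-arm changes are descriptive.

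The cost is a few sentences and a weaker claim for hypothesis 1. Sample size, visits, measurements and treatment stay as they are.

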## Methods

2

### Study design

2.1

This study is a two-armed randomized controlled trial with follow-up at 6 months (Fig. 1). Data will be collected before the first cycle of chemotherapy (T0), after chemotherapy (T1), and 6 months later (T2). The primary outcome for this study is muscle fiber size. Secondary outcomes are: regulators of muscle fiber size and function, indicators of cellular stress and mitochondrial function, myokines with potential antitumor effects, muscle strength, and cardiorespiratory fitness. All outcomes are listed in Table 1.

**Figure 1 F1:**
[figure not shown]
Study flowchart.

**Table 1 T1:** Outcomes and assessments.

	Specific variable	Assessment	T0	T1	T2
Primary outcome					
Muscle fiber size	Muscle fiber CSA	Cross-sections of muscle fiber	x	x	x
Secondary outcomes					
*Regulators of muscle fiber size and function*					
Number of myonuclei and satellite cells per muscle fiber	Myonuclei/fiber, SC/fiber	Cross-sections of muscle fiber	x	x	x
Proteins involved in muscle protein synthesis and degradation	PI3K/Akt/mTOR-pathway; including but not limited to: mTOR, P70s6k, 4EBP1, eIF4A, FOXO Ubiquitin ligase E2, LC3 (I and II), p62, myostatin, as well as ubiquitinated proteins	Western blot	x	x	x
Indicators of cellular stress	Hsp27, αB-crystalline, Hsp60, Hsp70	Western blot	x	x	x
Mitochondrial function	Mitochondrial structure	Cross-sections and whole fiber preparations of muscle biopsies	x	x	x
	CS, Cox 4 and HAD	Western blot	x	x	x
*Myokines*					
Potential anti-tumor myokines	Including, but not limited to: IL-6, IL-15, SPARC, TWEAK, IL-8, IL-10, IL-1β, IFN-γ, TNF-α, TNFR1	mRNA levels by real-time PCR analyses and protein levels by Western blot and ELISA	x	x	x
*Muscle Strength*					
	Upper extremities	1RM, chest press.	x	x	x
	Lower extremities	1RM, single leg press	x	x	x
*Cardio-respiratory fitness*					
	VO_2max_	Maximal oxygen uptake test	x	x	x
*Body composition*					
	Fat free mass, Fat mass	BodPod, BIA	x	x	x
	Body mass index	Weight and height	x	x	x
*Biomarkers of oxygen transportation, stress, inflammation, metabolic outcomes and muscle damage*					
	Hemoglobin, serum-cortisol, HbA1c, blood lipids, CRP and CK-MB	Standardized clinical measures	x	x	x
*Sociodemographic*					
	Age, partnership, number and age of children living at home, education, income, work and sick leave	Study-specific questionnaire	x		
*Lifestyle, quality of life and fatigue*					
	Dietary habits, alcohol consumption, tobacco use, motivation, self-efficacy and barriers to training. Health-related quality of life, Cancer related fatigue	Study-specific questionnaire, EORTC QLQ-C30, QLQ-BR25, MFI	x	x	x
*Physical activity*					
	Physical activity level	Sensewear Armband	x	x	x
*Disease and treatment*					
Disease specific information	Diagnosis Type, dose and side-effects of, and adherence to oncological treatment	Medical records			x
*Adverse events*					
	Adverse events occurring during exercise training sessions	Reported by coaches		x	x
	Adverse events occurring during muscle biopsy sampling	Reported by technicians	x	x	x

4EBP1 = Eukaryotic translation initiation factor 4E-binding protein 1, BIA = Bioelectrical impedance analysis, CK-MB = creatine kinase-myocardial band, Cox 4 = cytochrome c oxidase subunit 4, CRP = C-reactive protein, CS = citrate synthase, CSA = cross-sectional area, eIF4A = eukaryotic initiation factor-4A, EORTC QLQ-C30 = European Organization for the Research and Treatment of Cancer Quality of Life Questionnaire Core 30, HAD = 3-hydroxyacyl-CoA-dehydrogenase, Hsp27, 60 and 70 = heat shock protein 27, 60 and 70, IFN-γ = Interferon gamma, IL-6, -8, -10, -15, -1β = Interleukin- 6, -8, -10, -15 and 1beta, MFI = Multidimensional fatigue inventory, mTOR = mechanistic target of rapamycin, p62 = ubiquitin-binding protein p62, P70s6k = ribosomal protein S6 kinase, QLQ-BR25 = The European organization for research and treatment of cancer quality of life questionnaire, SC = satellite cell, SPARC = secreted protein acidic and rich in cysteine (Osteonectin), T0 = before start of chemotherapy and training intervention, T1 = after chemotherapy and training intervention, T2 = 6-month follow-up, TNF-α = tumor necrosis factor alpha, TNFR1 = tumor necrosis factor receptor 1, TWEAK = TNF-related weak inducer of apoptosis, VO^2^max = maximal oxygen uptake.

### Participant recruitment and eligibility criteria

2.2

Women recently diagnosed with breast cancer will be recruited from Uppsala University Hospital.

Eligibility criteria are:

1.women diagnosed with stage I-III breast cancer,2.>18 years old,3.literate in Swedish,4.scheduled to undergo (neo-)adjuvant chemotherapy with a combination of taxanes and anthracyclines or only 1 of these treatments.

Exclusion criteria are:

1.unable to perform basic activities of daily living,2.cognitive disorders or severe emotional instability,3.other disabling comorbidities that might hamper physical training (e.g., severe heart failure, chronic obstructive pulmonary disease, orthopedic conditions, and neurological disorders).

Eligibility will be assessed by treating surgeons or medical oncologists, and all eligible women will receive written information. Women who meet the inclusion criteria will be provided with further information about the study and written informed consent will be obtained by research staff. Based on the experience gained from on-going studies and previous relevant studies within the research group, an inclusion rate of 35% to 40% can be expected. The study was initiated in December 2018 and with the expected inclusion rate; the last participants will complete the intervention during the second half of 2021.

